## Abstract

**Background:**

Anxiety is a common mental health problem seen in primary care. However, its management in clinical practice varies greatly. Clinical practice guidelines (CPGs) have the potential to reduce variations and improve the care received by patients by promoting interventions of proven benefit. However, uptake and adherence to their recommendations can be low.

**Method/design:**

This study involves a community based on cluster randomized trial in primary healthcare centres in the Madrid Region (Spain). The project aims to determine whether the use of implementation strategy (including training session, information, opinion leader, reminders, audit, and feed-back) of CPG for patients with anxiety disorders in primary care is more effective than usual diffusion.

The number of patients required is 296 (148 in each arm), all older than 18 years and diagnosed with generalized anxiety disorder, panic disorder, and panic attacks by the Diagnostic and Statistical Manual of Mental Disorders-IV (DSM-IV). They are chosen by consecutive sampling.

The main outcome variable is the change in two or more points into Goldberg anxiety scale at six and twelve months. Secondary outcome variables include quality of life (EuroQol 5D), and degree of compliance with the CPG recommendations on treatment, information, and referrals to mental health services. Main effectiveness will be analyzed by comparing the patients percentage improvement on the Goldberg scale between the intervention group and the control group. Logistic regression with random effects will be used to adjust for prognostic factors. Confounding factors or factors that might alter the effect recorded will be taken into account in this analysis.

**Discussion:**

There is a need to identify effective implementation strategies for CPG for the management of anxiety disorders present in primary care. Ensuring the appropriate uptake of guideline recommendations can reduce clinical variation and improve the care patients receive.

**Trial registration:**

ISRCTN: ISRCTN83365316

## Background

### Normal and pathological anxiety

Anxiety is a common mental health problem seen in primary care. Anxiety can be defined as an anticipation of future harm or misfortune, accompanied by a feeling of unpleasantness and/or somatic symptoms of tension. This feeling is normal in the face of certain day-to-day stressing situations. When it exceeds a certain intensity or overwhelms a person's adaptive capacity, anxiety becomes pathological. Anxiety disorders are a group of illnesses characterized by the presence of worry, excess of fear or dread, tension, or activation that causes a notable uneasiness or a clinically significant deterioration of an individual's activity [1].

The causes of anxiety disorders are not entirely known, but biological factors, as well as environmental and psychosocial ones, are involved [2-4]. Some authors say that it is the interaction of multiple determining factors that favours the appearance of these anxiety disorders [5]. In addition, co-morbidity with other mental disorders, such as mood disorders, is very common [3-6].

The proper diagnosis, treatment, and, in those cases where necessary, appropriate referral of anxiety disorders to mental health services, is fundamental for effective clinical management [7,8].

### Anxiety as a health problem

The prevalence of anxiety disorders varies depending on different epidemiological studies, with prevalence-year and prevalence-life being set at between 10.6% and 16.6% [9]. Data for Spain from the European Study of the Epidemiology of Mental Disorders (ESEMeD) estimate a prevalence-year of 5.1% [10,11]. Mental disorders represent a burden for individuals, as well as for families and the community. In the case of the community of Madrid, neuropsychiatric illnesses are confirmed as the first cause of adjusted years of life for incapacity [12].

According to the World Health Organization's report on mental health, 20% of all patients attended by primary care professionals suffer one or more mental disorders. This report recommends that management and treatment be performed as far as possible in primary care so as to facilitate access to services for the greatest number of people possible [13].

### Clinical practice guidelines (CPGs) as a tool for the management of anxiety disorders in primary care

The diagnostic and therapeutic approach to these disorders varies widely. Primary care professionals have different grades of training in the area of mental health, in psychiatric interview skills, as well as in psychological intervention techniques [14-16].

A study in the United States between 1985 and 1998 described an increase in the use of psychopharmaceutical medication in primary care visits (38.7% compared with 54.6%) while, at the same time, it showed a constant drop in the use of psychological interventions (6.8% to 2%) in the treatment of anxiety disorders [17].

CPGs are a good tool to reduce this variability and improve evidence informed in the clinical decision-making. In Spain, the Ministry of Health and Social Policy has put into effect the 'Guiasalud' project [18] to draft CPGs. In the framework of this project, the *Clinical Practice Guideline for the Approach to Anxiety Disorders in Primary Care *has been drafted in coordination with the Technologies Assessment Unit of the Agencia Lain Entralgo [19].

The scope of the CPG covers the diagnosis and management of adult patients with generalized anxiety disorders (GAD) and panic disorder (PD), with or without agoraphobia, in the context of primary care.

Two aspects of this CPG development are worth noting. The first is the involvement of patients with anxiety disorders in all phases of the development process. The second is that the CPG includes interventions that can be carried out by the various professionals working in primary care. These interventions are carried out at the primary healthcare centers, mainly by nursing and/or social workers [19]. Likewise, it is worth noting the low utilization of psychological interventions of proven effectiveness [20]. Our group has carried out a study that focuses on the evaluation of the effectiveness of the intervention groups directed by nurses in patients with anxiety in primary care [21].

The Goldberg Anxiety and Depression Scale (GADS) has been included in the guideline to evaluate the changes obtained by the various interventions and as a way to provide key questions to guide the clinical interview. This scale has been chosen because it is brief and easy to manage and interpret [22-24]. The Spanish version has demonstrated its reliability and validity within the ambit of primary care, and it has the right sensitivity (83.1%), specificity (81.8%), and positive predictive value (95.3%) [25].

### Strategies to implement CPGs

CPGs will only be useful for professionals and patients if their recommendations are incorporated to regular clinical practice. Achieving this is a complex process in which several factors play a role [26,27].

To increase the use of the guideline, its distribution and implementation strategy must be planned very carefully. As a first step, the identification of the barriers and facilitating factors, adapting all strategies to the setting in which the CPGs will be used, is fundamental [28-30].

Several CPGs implementation strategies have demonstrated their effectiveness. Some authors group these interventions depending on whom they are addressed to: physicians and patients, communities or the general population, or health centres and/or health systems [31].

The Cochrane EPOC (Effective Practice and Organization of Care) group proposes to classify interventions into four categories: professional interventions (such as distribution of educational materials or educational meetings); financial interventions (such as fee-for-service or prospective payment); organisational interventions (such as creation of clinical multidisciplinary teams) and regulatory interventions (any intervention that aims to change health services delivery or costs by regulation or law) [32].

The Grimshaw [33]*et al*. review evaluates the effectiveness and cost of different clinical practice guideline dissemination-implementation organizational strategies. This study takes into account the impact on professionals as well as on patients. It includes 235 studies (between 1966 and 1998) and 309 comparisons. Among the results, it is worth noting that most implementation strategies improved adherence to CPGs. Simple strategies, such as reminders, increase adherence by 14.1%. The distribution of educational materials improves this by 8.1%. Educational programmes, almost always as components of more complex interventions, improved practice by 6%, and audits and feedback by 7%. The complexity of the strategies and the mixture of interventions did not improve results. In their conclusions, it is noted that there is little evidence about which strategies can be more effective in each situation. The authors consider that there is a need to develop and validate theoretical models for behavioural change, as well as to investigate the efficiency of the strategies in the presence of different barriers and factors that can modify effectiveness.

We consider it fundamental to put into effect organizational strategies that will enable us to use the guideline and apply its recommendations, as well as to measure and evaluate the impact that implementation of the CPGs will have on professionals modifying their practices, and improving outcomes for patients [34,35].

There are two reasons for using cluster randomised trials design: to evaluate the group effect of an intervention; and to avoid 'contamination' across interventions when trial participants are managed within the same setting.

### Main objective

The aim of the present work is to determine whether the use of a CPG implementation strategy (including training session, information, opinion leader, reminders, audit, and feed-back) for patients with anxiety disorders in primary care is more effective than usual diffusion in improving the score of the Goldberg anxiety scale at six and twelve months.

### Secondary objectives

1. Evaluate the effectiveness of a CPG implementation strategy for the management of patients with anxiety disorders compared with the regular strategy, measured as the degree of suitability of the treatments (psychological, pharmacological, *et al*.) received by patients.

2. Evaluate the effectiveness of a CPG implementation strategy for the management of patients with anxiety disorders compared with the regular strategy, measured as the percentage of patients who have received the information proposed in the guideline (oral or written) about their disorder.

3. Evaluate the effectiveness of a CPG implementation strategy for the management of patients with anxiety disorders compared with the regular strategy, measured as the degree of suitability of referral to mental health services, based criteria established in the guideline.

4. Describe the professionals' opinion about the usefulness of the CPG.

5. Evaluate the effectiveness of a CPG implementation strategy for the management of patients with anxiety disorders compared with the regular strategy measured as a change in the patient's quality of life.

## Methods/design

### Design of the study

This study is a two-year community, parallel clinical trial, randomised by clusters, that compares two different CPG implementation strategies. The intervention will be made on health professionals (physicians, nurses, and social workers) of primary healthcare centres (PHCC) in the region of Madrid, Spain. The randomization units will be PHCCs (clusters). The units of analysis are patients of health professionals (individual level) of the PHCCs participating in the study (as a control or intervention) according to the CONSORT checklist (additional file 1).

### Subjects of the study

Subjects older than 18 years of age, who visit primary care because of symptoms compatible with anxiety disorders at PHCCs in the region of Madrid, and those who have been diagnosed with anxiety disorders according to Statistical Manual of Mental Disorders-IV (DSM-IV) criteria [1].

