### Inclusion criteria

Agree to participate in the study and written informed consent.

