### Exclusion criteria

1. Subjects diagnosed with anxiety for post-traumatic stress, acute stress disorders, anxiety disorders induced by substances, organic anxiety disorders.

2. Subjects who cannot read or understand Spanish.

3. Subjects who will not reside in the basic area in the year following their inclusion in the study.

4. Immobilized or institutionalized patients.

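### Eligibility is defined in two incompatible ways, and the wider one could admit patients outside the scope of the guideline being implemented

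*Protocol article*

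**What the plan says.** The protocol article describes its patients in several places.

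- **Abstract, Method/design:** patients are adults "diagnosed with generalized anxiety disorder, panic disorder, and panic attacks by the Diagnostic and Statistical Manual of Mental Disorders-IV".
- **Background, section on guidelines as a tool:** the guideline covers "adult patients with generalized anxiety disorders (GAD) and panic disorder (PD), with or without agoraphobia, in the context of primary care".
- **Subjects of the study:** the diagnostic clause reads "those who have been diagnosed with anxiety disorders according to Statistical Manual of Mental Disorders-IV (DSM-IV) criteria". It follows a clause about adults who consult at the participating centres with symptoms that could indicate such a disorder.
- **Inclusion criteria:** one entry only, "Agree to participate in the study and written informed consent".
- **Exclusion criteria, item 1:** "Subjects diagnosed with anxiety for post-traumatic stress, acute stress disorders, anxiety disorders induced by substances, organic anxiety disorders". The other three items concern language, residence, and being immobilised or institutionalised.

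Under Concealment of allocation, patients are checked against the inclusion and exclusion criteria. Under Secondary objectives, items 1 to 3 concern suitability of treatment, receipt of the information the guideline proposes, and suitability of referral by the guideline's criteria.

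**The concern.** The abstract gives a closed list of diagnoses. The eligibility sections give an open class with four categories removed, and the open class is wider than both the abstract's list and the guideline's scope.

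Three things are at stake.

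1. **Secondary outcomes.** Objectives 1 to 3 evaluate care received against this guideline. For a patient with a disorder it does not cover, it is unclear what counts as suitable treatment, proposed information or suitable referral.
2. **Size of the effect.** If the implementation strategy does less for such patients, their presence pulls the difference in Goldberg response towards zero.
3. **Comparability of arms.** Centres are randomised first; patients are then enrolled by their own unblinded professionals. Under Intervention, only the intervention group is trained on diagnosis, including telling anxiety as a symptom from anxiety as a disorder. A loose diagnostic entry rule leaves the case mix free to differ by arm.

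**Working it through.** **Step 1: the texts side by side**

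| Source | Diagnoses admitted |
|---|---|
| Abstract | Generalised anxiety disorder, panic disorder, panic attacks |
| Guideline scope (Background) | Generalised anxiety disorder; panic disorder with or without agoraphobia |
| Subjects of the study | DSM-IV anxiety disorders, type not limited |
| Inclusion criteria | No diagnosis named |
| Exclusion criteria | Removes post-traumatic stress, acute stress, substance-induced and organic anxiety |

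A patient with a DSM-IV anxiety disorder that is neither generalised anxiety nor panic, and not among the four exclusions, satisfies the last three rows and fails the first two. The check under Concealment of allocation, applied to the listed criteria, would pass this patient. The exclusion list points the same way: excluding those four categories is needed only if the starting population is wider than generalised anxiety and panic. Panic attacks appear in the abstract but are not named in the guideline's scope.

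**Step 2: the plan's own sample size**

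Inputs from Sample size: alpha 0.05, power 80%, difference 20% (read here as 20 percentage points), ICC 0.01, mean cluster size 20, loss 20%. The control rate is not stated; 50% v 70% (or 30% v 50%) is assumed.

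- Two proportions, two-sided, no continuity correction: 93 per arm. With continuity correction: 103 per arm, as stated.
- Design effect: 1 + (20 − 1) × 0.01 = 1.19; 103 × 1.19 = 122.57, rounded up to 123.
- Loss added as a multiplier: 123 × 1.20 = 147.6, rounded up to 148 per arm, 296 in all, as stated.

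So the stated figure is reproduced; the present point does not depend on it.

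**Step 3: illustration of dilution**

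- Evaluable per arm: 148 × 0.8 = 118.4.
- Evaluable per centre: 2 × 118.4 / 16 = 14.8.
- Design effect: 1 + (14.8 − 1) × 0.01 = 1.138.
- Effective number per arm: n = 118.4 / 1.138 = 104.0.

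Let q be the share of patients outside the guideline's scope and r the fraction of the full effect they receive. The expected difference is d = 0.20 × [1 − q(1 − r)], with p1 = 0.50, p2 = 0.50 + d and p̄ their mean.

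Power = Φ{ [d − 1.96 √(2p̄(1 − p̄)/n)] / √((p1(1 − p1) + p2(1 − p2))/n) }

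At q = 0: [0.20 − 1.96 × 0.0679] / 0.0665 = 1.006, so power is 0.843. This exceeds 80% because the test here has no continuity correction.

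| q | d, r = 0 | Power, r = 0 | d, r = 0.5 | Power, r = 0.5 |
|---|---|---|---|---|
| 0 | 0.20 | 84% | 0.20 | 84% |
| 10% | 0.18 | 76% | 0.19 | 80% |
| 20% | 0.16 | 65% | 0.18 | 76% |
| 30% | 0.14 | 53% | 0.17 | 70% |

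With a 30% control rate, 103 per arm and no effect outside scope, the results are close: 84%, 76%, 66% and 55%.

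**The case against.** The best defence is that the abstract specifies what the Methods state generally: its three conditions are themselves anxiety disorders or presentations, and recruiters may apply that list. The article is condensed, and the electronic log is not shown. This stands against any claim that off-guideline patients would certainly be enrolled. It does not remove the conflict, because the criteria against which patients are checked name no qualifying diagnosis.

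A reader might also infer that symptoms alone suffice for entry. The sentence under Subjects of the study allows that reading, but symptoms plus a DSM-IV diagnosis is equally natural, and the abstract requires a diagnosis. It is an ambiguity of wording and no more.

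A reader might infer that patients outside the scope cannot benefit. The documents do not support this. Much of the intervention is not specific to one diagnosis (interview skills, bibliotherapy, groups on breathing, relaxation, exercise and sleep), and the primary outcome is a general anxiety subscale. Zero effect is therefore the pessimistic end of a range.

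Finally, the Discussion discloses part of the bias. It concedes difficulty with specific diagnoses, which it expects the guideline to reduce; it mentions training of all participating professionals; and it plans to compare decliners by arm. Diagnosis is also recorded for each patient, so off-guideline patients could be identified at analysis. These points soften the concern. But comparing decliners does not show whether diagnostic mix differs among those enrolled, and the training on diagnosis is listed for the intervention group only.

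**Conclusion.** The point holds as an internal contradiction: the abstract and the eligibility sections define different populations, and the wider one exceeds the guideline's scope. Patients outside that scope could be enrolled, and objectives 1 to 3 are not clearly defined for them.

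The size of any dilution is unknown. The power figures describe scenarios and do not measure a loss. They rest on an assumed share outside scope, an assumed effect in those patients and an assumed control rate, none of which the document gives. Within the range shown, a 10% share takes power from 84% to between 76% and 80%, and a 30% share to between 53% and 70%. Unequal dilution by arm is possible under this design but cannot be quantified from the document.

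**What to change.** Reconcile the abstract, the statement of guideline scope, Subjects of the study, and the inclusion and exclusion criteria into one positive diagnostic inclusion criterion that matches the guideline's scope. In doing so:

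- have the sponsor settle whether panic attacks are covered, since the abstract includes them and the stated scope does not name them;
- if symptoms plus a DSM-IV diagnosis is intended, say so explicitly under Subjects of the study;
- use the same list of diagnoses in the electronic log, so that the eligibility check tests it.

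The cost is protocol wording and one field in the log. The downside is somewhat fewer eligible consultations per centre and slightly narrower applicability, which matters because the Discussion counts applicability in regular practice as an advantage of enrolment by the professionals themselves.

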### Inclusion criteria

Agree to participate in the study and written informed consent.

### Exclusion criteria

1. Subjects diagnosed with anxiety for post-traumatic stress, acute stress disorders, anxiety disorders induced by substances, organic anxiety disorders.

2. Subjects who cannot read or understand Spanish.

3. Subjects who will not reside in the basic area in the year following their inclusion in the study.

4. Immobilized or institutionalized patients.

### Sample size

#### Method of calculation

For an alpha of 0,05, a power of 80% and in order to detect a decrease in the Goldberg Scale (two or more points) of 20% in the intervention group, the overall simple size required 206 patients (103 in each arm of the study). Because randomisation was by cluster, the sample size had to be larger than if simple randomisation had been performed, in order to take into account the design effect (DE). The DE was calculated as follows: DE = 1 + (n_c _- 1) * ICC (where n_c _is the mean number of individuals in the cluster, and ICC the intracluster correlation coefficient) [36]. The ICC in the present work was deemed to be 0.01. The mean cluster size was assumed to be 20 patients. Given these assumptions, and expecting a 20% loss rate, the final sample size required was 296 patients (148 in each arm).

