### Sequence generation

The 16 PHCCs will be assigned to the intervention or the control group following a simple, computer-generated random sequence (EPIDAT 3.1).

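### The printed sample-size inputs lead to 308 patients, not 296; the effect on power is small, and restating the paragraph settles it

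*Protocol article*

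**What the plan says.** The calculation is in the Protocol article under Methods/design, Sample size (Method of calculation).

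- **Error rates and effect:** "For an alpha of 0,05, a power of 80"%, "in order to detect a decrease in the Goldberg Scale (two or more points) of 20% in the intervention group".
- **Before adjustment:** "the overall simple size required 206 patients (103 in each arm of the study").
- **Clustering:** the design effect is DE = 1 + (n_c - 1) x ICC, where n_c "is the mean number of individuals in the cluster, and ICC the intracluster correlation coefficient". The ICC is set at 0.01, and "The mean cluster size was assumed to be 20 patients".
- **Result:** "Given these assumptions, and expecting a 20% loss rate, the final sample size required was 296 patients (148 in each arm").

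The Abstract (Method/design) repeats the total: "The number of patients required is 296 (148 in each arm"). The number of clusters appears under Sequence generation: "The 16 PHCCs will be assigned to the intervention or the control group". The sample-size section does not show the loss step, and it does not say whether the 20 patients per cluster are counted before or after loss.

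**The concern.** The section prints the starting size, the design-effect formula, its two inputs and the loss rate, and says that 296 follows from them. Taken in order, with the loss handled so that the required number is still there at analysis, they lead to a larger total. The gap is the one that appears when a 20% loss is allowed for by adding 20% to the target instead of dividing by 0.8. Adding 20% falls short, because 20% of the enlarged number is then lost: 1.2 x 0.8 = 0.96.

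The total is a headline figure that appears twice in the article. A reader who checks it should be able to reach it from the inputs given. If it is too small for those inputs, the 80% power claimed for the primary comparison is slightly overstated.

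**Working it through.** **Inputs.** From the sample-size section: 103 per arm (206 in total), n_c = 20, ICC = 0.01, loss 20%, alpha 0.05, power 80%. From Sequence generation: 16 centres. Assumed here because the article does not give them: a two-sided test, and response proportions of 50% v 70% for the 20-point difference.

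**Step 1: the starting size.** Two-proportion formula at 50% v 70%: (1.960 x √(2 x 0.6 x 0.4) + 0.842 x √(0.25 + 0.21))² / 0.2² = 93 per arm. With continuity correction this becomes 103, as printed. 30% v 50% gives the same, while 40% v 60% gives 97 and 107.

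**Step 2: the design effect.** DE = 1 + 19 x 0.01 = 1.19. Then 103 x 1.19 = 122.57 per arm, or 245.14 in total.

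**Step 3: reproducing 296.** Two routes come close.
- Multiplying by 1.2: 122.57 x 1.2 = 147.08, rounded up to 148 per arm, 296 in total.
- Taking 20 as the enrolled cluster size, so that 20 x 0.8 = 16 are analysed: DE = 1 + 15 x 0.01 = 1.15, and 206 x 1.15 / 0.8 = 296.1 (148.06 per arm, which must be rounded down to give 148).

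**Step 4: the printed inputs with the usual loss adjustment.** 122.57 / 0.8 = 153.2, so 154 per arm or 308 in total. On the unrounded total, 245.14 / 0.8 = 306.4, so 307. The printed 296 is 11 to 12 patients below these, about 4%. At DE 1.19, 296 covers a loss of up to 1 - 245.14/296 = 17.2%.

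**Step 5: what 296 gives.** After 20% loss, 148 x 0.8 = 118.4 per arm are analysed. Effective size per arm is 118.4 / DE. Power is scaled from the plan's own base (103 per arm = 80%) as Φ(2.802 x √(effective n / 103) - 1.960).

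| Cluster size in the DE | DE | Effective n per arm | Power |
|---|---|---|---|
| 20, as printed | 1.19 | 99.5 | 78.6% |
| 18.5 (296/16, enrolled) | 1.175 | 100.8 | 79.1% |
| 16 (20 less 20%) | 1.15 | 103.0 | 80.0% |
| 14.8 (296 x 0.8/16, analysed) | 1.138 | 104.0 | 80.4% |

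The continuity-corrected formula at 50% v 70% also gives 78.6% in the first row.

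**Step 6: the requirement with the analysed cluster size.** 206 x 1.138 / 0.8 = 293.03, so 294 with equal arms. 296 is enough on this basis.

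**The case against.** The strongest reply is that the article never says a factor of 1.2 was used. If 20 is the enrolled cluster size, the article's own formula with 16 analysed per cluster and division by 0.8 gives 296.1. That route is legitimate, and it means the source of 296 cannot be established from the text. It does not make the paragraph right as printed: the section defines n_c as the mean cluster size, sets it to 20, and mentions no smaller value after loss.

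A reader might infer that the trial is underpowered. The documents do not support that. The shortfall is 1.4 points on the least favourable reading and disappears when the design effect uses the number analysed per centre. The 78.6% also rests on a continuity-corrected calculation, while the Statistical analysis section names a chi-squared test without mentioning a correction. Uncorrected, 99.5 effective patients per arm give 82.6% at 50% v 70% and 81.0% at 40% v 60%.

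A reader might also see a contradiction between 16 centres of 20 (320 patients) and 296 patients (18.5 per centre). The 20 is a planning assumption for the design effect, not a recruitment target, and a value above 18.5 errs on the safe side because it raises the design effect. The mismatch only shows why the value used should be stated.

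The control-arm response behind the 103 is also not given, but that is detail an article may leave to the full protocol, and the point does not depend on it.

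**Conclusion.** The point holds as a minor error in a stated figure. On a plain reading of the printed inputs (103 per arm, design effect 1.19, 20% loss) the requirement is 308, and 296 is about 4% below it. Multiplication by 1.2 instead of division by 0.8 fits the printed number, but it remains an inference.

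The consequence is small: power lies between about 78.6% and 80.4%, depending on which cluster size enters the design effect. These figures assume a two-sided test and take the plan's 103 per arm as giving 80%. They take the ICC of 0.01 and the 20% loss as stated. The difference from 308 does not depend on the response proportions.

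**What to change.** Restate the sample-size paragraph so that the total follows from what is printed. No further patients are needed.

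- **Preferred:** keep 296, show the division by 0.8, and state the cluster size and design effect used. With 16 centres that is 18.5 enrolled and 14.8 analysed per centre and a design effect of 1.138, which requires 294 with equal arms.
- **If a design effect of 1.19 is kept:** state that the requirement is 308 (154 per arm), or that 296 gives slightly under 80% power at a 20% loss.

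In either case, say whether the mean cluster size is counted before or after loss, and make the Abstract agree. The cost is one corrected paragraph, plus the Abstract figure if the stated requirement changes. The design and the analysis are unaffected.
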